#### Randomization

We used a computer program to randomize the three experimental groups and four fibromyalgia associations, taking into account the size of each center
[40]. The 449 participants were allocated to the three experimental groups as follows: CG = 154, IG = 153 and MIG = 142 (Table 
1). We applied another computer program to generate random sequences to select the participants from each fibromyalgia association for the experimental and control groups
[41]. The randomization results will be checked by analyzing potential confounders such as walking patterns, physical activity, impact of FM, pain, emotional status and age (see the “Statistical analysis” subsection below).

**Table 1 T1:** **Randomized experimental group-center assignments**^
**a**
^

**Patient associations**	**Assignment, **** *n * ****(%)**			**Total**
	**CG**	**IG**	**MIG**	
ADEFA	7 (28.0)	9 (36.0)	9 (36.0)	25 (100)
AFEFE	42 (39.6)	29 (27.4)	35 (33.0)	106 (100)
AFIBROM	73 (33.2)	87 (39.5)	60 (27.3)	220 (100)
AFIBROTAR	32 (32.7)	28 (28.6)	38 (38.8)	98 (100)
Total	154 (34.3)	153 (34.1)	142 (31.8)	449 (100)

^a^ADEFA: Fibromyalgia Association of Alicante; AFEFE: Fibromyalgia Association of Elche; AFIBROM: Fibromyalgia Association of Madrid; AFIBROTAR: Fibromyalgia Association of Talavera de la Reina (Toledo); CG: Control group; IG: Implementation intention group; MIG: Motivation and implementation intention group.

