This triple-blind study includes masking of the following groups in the manner described. Participants will know only that there are different intervention sessions but will not know the session contents; moreover, they will be unaware of the assumptions regarding the superiority of one intervention over another. Measures will be taken by researchers who do not participate in the treatment application and who are blinded to the experimental conditions. The statistician will also be blinded to the study protocol. The researchers who apply implementation intentions will also be blinded with respect to the MIG or IG experimental condition. In this phase, we aim to study the efficacy of the MIG intervention on unsupervised walking over the short term (7 weeks), medium term (3 months) and long term (9 months). The measurement at 7 weeks will be taken during the week after completion of the 6-week minimum walking program. We will base the selection of the medium- and long-term measurements on the assumption that the highest percentage of dropouts occurs between 3 and 6 months in supervised physical exercise programs
[8,9]. On the day of the intervention, a researcher will be responsible for the distribution of the participants into the three different treatment groups following random assignment. The researcher will remind participants of their confidentiality commitment.

Our main hypothesis is that a combined intervention (both motivational and volitional) will significantly increase walking behavior in comparison to the control group and that this effect will be higher than that in a merely volitional intervention in the short term and stable in the medium and long term.

Our selected walking pattern for FM patients is between two and four times weekly for about 50 minutes in bouts of 15 to 20 minutes, with a small rest between bouts to allow patients to avoid fatigue and continue the activity, for a minimum of six consecutive weeks

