### Study population and recruitment process

The fibromyalgia associations of Alicante (ADEFA), Elche (AFEFE), Madrid (AFIBROM) and Talavera de la Reina (AFIBROTAR) collectively comprise a total of 2,438 members with a clinical diagnosis of FM (75.8% diagnosed by rheumatologists, 9.2% by general practitioners, 5.3% by traumatologists, 2.2% by clinical rehabilitation specialists, 0.7% by neurologists and 6.7% by clinicians in other specialties). Slightly more than half (51.4%) of the sample are receiving psychological treatment because of FM. To select our reference population (women between 18 and 70 years of age who meet the London Fibromyalgia Epidemiology Study Screening Questionnaire criteria for fibromyalgia (London-4) ), we first used the associations’ records to select the members who met the two first criteria (*n* = 2,227). We then sent letters to these 2,227 women with information about the study, together with informed consent forms, the London Fibromyalgia Epidemiology Study Screening Questionnaire
[34,35] and other questionnaires covering the remaining variables related to the sample characteristics and participation criteria. As we do not have a second clinical diagnosis confirmation, the London-4 criteria were used to ensure population homogeneity. Although these criteria screen only for widespread musculoskeletal pain and do not take into consideration other clinical aspects of FM, they give an optimal sensitivity (100%) in FM screening population studies and good positive predictive values for women in rheumatology settings
[35].

A total of 972 questionnaires (43.5%) were returned in two runs. The eligibility criteria were then applied, and our selected reference population subsequently consisted of 920 members with FM (44 did not fit the London-4 criteria and 8 questionnaires did not contain enough data). The remaining criteria were that the individual did not walk or the walking pattern did not comply with one or more features of the selected walking program, the individual was without comorbidity which impeded walking or, if there was comorbidity, the individual had received medical advice to walk. A total of 582 members (63.3%) satisfied these criteria. Figure 
1 is a flowchart of the participant recruitment process.

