#### Sample size calculation

We calculated the sample size for the experimental study by taking into consideration the 582 FM participants previously identified as the eligible population derived from the different associations: ADEFA (*n* = 33, 5.7%), AFEFE (*n* = 125, 21.5%), AFIBROM (*n* = 314, 54.0%) and AFIBROTAR (*n* = 110, 18.9%). The expected differential increase in the selected exercise prevalence from baseline is 10% for CG, 20% for IG and 40% for MIG. Given the rule that the frequency of dropouts should not exceed the frequency of the effect, we expect a maximum dropout rate of 30% before random allocation. This percentage will be added to the calculated sample size. We have defined the risk α as 5% and the study power as 80%. The minimum magnitude of the expected effect (in relation to the effect on CG) is 10% for IG and 30% for MIG. After we apply these conditions and dividing the sample population into three experimental groups, each group will consist of 115 persons, which is equal to 345 participants. In previously reported supervised programs of moderate-intensity walking, adherence has ranged from 62%
[14] to only 37.5%
[32]. In other studies, the percentage of patients who finished the supervised program was greater than 70% to 80%
[7,15,36-39]. In other words, studies have shown that more than 20% to 60% of patients do not complete physical activity programs which include walking. Therefore, we added a 30% dropout rate as a reasonable calculation, which gives us a sample size of 449 women with FM.

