All eligible individuals were contacted (*N* = 582) because of the difficulties involved in the participation of the first 449 selected women, such as the failure to contact them after repeated attempts, nonattendance after three citations and distance of residence from the study location. Ultimately, 274 patients accepted and attended the first evaluation session (participation rate = 47.1%). No significant differences were found between these 274 participants and women with FM who did not participate in this phase of the study (*n* = 308) on the basis of any of the above-mentioned variables (age: *t* = 0.767, *P* = 0.443, df = 579; education level: χ^2^ = 5.567, *P* = 0.135; df = 3; employment status: χ^2^ = 7.567, *P* = 0.272, df = 6; pain intensity perception: *t* = 0.389, *P* = 0.697, df = 579; fatigue: *t* = -0.178; *P* = 0.858, df = 576; fatigue upon waking: *t* = 0.785, *P* = 0.433, df = 576; impact perception of fatigue: *t* = 0.410, *P* = 0.410, df = 577; cognitive problems: *t* = -0.718, *P* = 0.473, df = 577; impact perception of cognitive problems: *t* = -0.939, *P* = 0.348, df = 577; impact perception of sleeping disorders: *t* = -0.107, *P* = 0.915, df = 577). The groups showed different medians of moderate activities (*P* ≤ 0.01), but similar medians in total activity (*P* = 0.066), sitting (*P* = 0.208), walking (*P* = 0.609) and vigorous activities (*P* = 0.115). In addition, the groups presented a proportion of noncompliance similar to that of the total unsupervised pattern (45.8% and 44.2%, respectively) and the same proportion reported for medical recommendation to walk (81.8% in each group) (Table 
5).

Internal consistency analysis will be performed for the different scales using the Cronbach’s α coefficient. Path analysis will be conducted to identify the relative weights of attitudes, perceived norms and perceived behavioral control in the prediction of the behavioral intention (path coefficients). Furthermore, we will test the role of the fear of movement, pain and FM impact. Spearman and Pearson correlations and cross-tabulation analysis (depending on the variables) will be used to explore the agreement of the behavioral measurements.

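### The only allocation described covers 449 selected women, not the 274 who attended, so Table 1 cannot serve as the allocation of the enrolled women

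*Protocol article*

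**What the plan says.** Four parts of the protocol article bear on who is randomised and when.

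- **Sample size calculation.** The target is 345 women (115 per arm), raised by 30% to 449. On the timing of the loss it says "we expect a maximum dropout rate of 30% before random allocation".
- **Randomization.** In the past tense: "The 449 participants were allocated to the three experimental groups as follows: CG = 154, IG = 153 and MIG = 142". Table 1 breaks these counts down by association. A second program was used to "generate random sequences to select the participants from each fibromyalgia association for the experimental and control groups", so choosing women and giving them an arm appear to be one step.
- **Statistical analysis, Phase I.** All 582 eligible women were contacted "because of the difficulties involved in the participation of the first 449 selected women". The reasons given are failed contact, repeated non-attendance and distance. The outcome was: "Ultimately, 274 patients accepted and attended the first evaluation session".
- **Description of the overall project.** On the intervention day "a researcher will be responsible for the distribution of the participants into the three different treatment groups following random assignment". It does not say which assignment is meant.

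The Discussion adds that 180 women who missed the session without refusing will be contacted again. No section describes an assignment for eligible women outside the 449, or a randomisation of the 274.

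**The concern.** An allocation should cover the women who enter the trial. Here the only one described covers a different set, drawn up before acceptance and attendance were known. Some women on it are absent, and some women present may not be on it.

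If Table 1 governs the intervention day, two things follow. The arms contain only those listed women who attended after being assigned, and any woman from outside the list reaches an arm by an unstated route. The list also existed while recruitment was going on. The article says that participants, outcome assessors, the statistician and the researchers who deliver implementation intentions are masked. It does not mention the staff who contacted and invited women, so the text does not secure concealment from them.

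The safeguard offered is a baseline comparison, with adjustment for measured confounders. That cannot stand in for a valid allocation, because it does not reach unmeasured differences such as readiness to travel or to respond to an invitation. Every between-arm comparison in phase II depends on this step.

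**Working it through.** **Inputs.** 345 and 30% (Sample size calculation); 449 = 154 + 153 + 142 (Randomization, Table 1); 582 eligible ("A total of 582 members (63.3%) satisfied these criteria"); 274 attenders (Statistical analysis, Phase I); 180 to be contacted again (Discussion).

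**1. The plan's own figure.** 345 × 1.30 = 448.5, rounded up to 449. The Table 1 rows give 25 + 106 + 220 + 98 = 449 and the columns give 154 + 153 + 142 = 449. The 449 allocated are therefore the inflated number, with the 30% allowance inside it.

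**2. Timing.** If losses come before allocation, those allocated should be whoever remains of the 449. The Randomization section allocates all 449. Both statements cannot describe the same procedure.

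**3. Eligible women outside the list.** 582 − 449 = 133. By association: ADEFA 33 − 25 = 8; AFEFE 125 − 106 = 19; AFIBROM 314 − 220 = 94; AFIBROTAR 110 − 98 = 12. These add up to 133.

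**4. Listed women not among the 274.** The article does not say how many attenders came from the list, so only bounds are available.

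| Case | Attenders from the list | Listed women absent | Attenders with no Table 1 arm |
|---|---|---|---|
| All 274 from the list | 274 | 449 − 274 = 175 (39.0%) | 0 |
| All 133 outsiders attended | 274 − 133 = 141 | 449 − 141 = 308 (68.6%) | 133 (133/274 = 48.5%) |
| Equal attendance on and off the list (assumption) | 274 × 449/582 ≈ 211 | 449 − 211 = 238 (53%) | 274 × 133/582 ≈ 63 (23%) |

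**5. Effect of contacting the 180 again.** Assume that they are among the 582 − 274 = 308 non-participants. If every one attended, the total would be 274 + 180 = 454. That exceeds 449, so at least 5 attenders would still lie outside Table 1. The 39.0% is a position at one time point and could fall.

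**6. Table 1 balance.** Association by arm gives chi-square 8.67 on 6 degrees of freedom, p = 0.19. The uneven cells, such as 87 IG against 60 MIG in AFIBROM, are compatible with chance.

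**The case against.** Most of the case on the other side limits how far the point can go.

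- **Consent.** A reader might infer that women were allocated before any contact or consent. The documents do not support that. The recruitment section says "We then sent letters to these 2,227 women with information about the study, together with informed consent forms", the eligible women are drawn from those who returned questionnaires, and consent is reported for each participant. Its timing relative to allocation is not given. What is supported is that allocation preceded acceptance of, and attendance at, the evaluation session.
- **Permanent loss.** A reader might take the absent 39% as lost to the trial. The figure refers to the first evaluation session, and 180 women are to be approached again.
- **Bias.** Non-attendance biases the comparison only if it is related to arm. None of the stated reasons mentions arm, and participants do not know the session contents. Losses before the arm is known cost precision and generalisability, but do not by themselves confound the arms. Nothing says that recruiters used the list.
- **Silence.** The article does not rule out a later random assignment of the added women. The flowchart is not shown, and an article may leave such mechanics to the full protocol.
- **Imbalance.** The uneven arm counts are chance variation and not an error.
- **Timing of a remedy.** The last measurement is at week 43 and completion is expected by the end of June 2014. If week 43 counts from the intervention, sessions were due by about early September 2013, before the article appeared in April 2014.

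All of this stands, but it does not remove the defect. The gap is more than omitted detail: the article states a completed allocation for the wrong set of women, and two of its sections conflict on whether losses precede it.

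**Conclusion.** The point holds in a limited form. Table 1 cannot be the allocation of the enrolled women. At the first evaluation session at least 175 of the 449 allocated women (39.0%, at most 68.6%) had not attended, and between 0 and 133 of the 274 attenders have no Table 1 assignment. The bounds need no assumption beyond the article's counts. The figure of about 63 attenders rests on equal attendance on and off the list.

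It would go too far to conclude that randomisation has failed or that protection against selection bias is lost. The documents show that this protection is not assured, because the route from the 449 to the women who receive an intervention is not described and the stated order of loss and allocation conflicts. Since every between-arm comparison relies on that route, it should be settled before the phase II analysis.

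**What to change.** 1. Reconcile Description of the overall project, Sample size calculation, Randomization and Statistical analysis (Phase I) so that they give a single order of events: selection, consent, attendance, baseline, allocation.
2. Relabel the 449 and Table 1 as a sampling frame.
3. Randomise women who have consented and attended after the phase II baseline, stratified by association. Keep the list concealed from those recruiting until the intervention day. This agrees with the statement that losses come before allocation.
4. Define the analysis population as everyone so randomised.
5. If any sessions have already run under Table 1, keep those assignments, report how women outside the list were assigned, apply the new list to any women remaining, and treat allocation batch as a stratum in the analysis.

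The cost is one computer-generated list and about a paragraph of text, with no added visits or participants. If all sessions have already run, only the reporting and the batch term in step 5 remain possible, and the uncertainty about the added women has to be stated as a limitation.

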### Interventions

In previous studies in the reviewed literature, we found that interventions for the promotion of walking have been heterogeneous and that no single method has proved to be more effective than others
[33]. One of the main advantages of our study is that the intervention is based on two well-established theories for predicting behavior. Following the procedures described in previous research
[42,43], all participants will receive information about the benefits of physical exercise in relation to their FM, and they will be asked to engage in the selected walking criteria. In addition, MIG participants will receive motivational interventions, and both the MIG and IG groups will receive information on the positive effects of making plans, specifying (1) days, (2) specific times of day, (3) location (for example, close to work, around the neighborhood) and (4) duration of the exercise (starting from the established minimum). Thus, they will be requested to write a specific individualized plan. The estimated duration of the intervention in each group is 90 minutes, conducted in only one group session with a maximum of 10 people. Figure 
2 shows the schedule for the intervention day.

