#### Phase II (second and third years)

As our main outcome is a binary variable, backward stepwise logistic regression analysis will be applied. This method will allow us to investigate whether the experimental condition is associated with the acquisition of the walking pattern. Analysis will be performed for each time measure. Changes in walking behavior over time will be analyzed by applying a Cox proportional hazards regression model for recurrent events. Using this methodology, we will estimate the hazard function of the outcome measure (the likelihood of walking over time). We will analyze differences between groups by introducing the experimental condition as a predictor of the moment in the longitudinal study when women maintained the walking pattern.

Randomization results will be checked to ensure that groups are comparable at the beginning of the study in terms of their distribution of potential confounding factors (walking pattern, IPAQ, FIQ, pain, age, emotional status and behavioral intention). The potential confounders will be selected according to previous analyses at baseline by applying confusion criteria (associations with exposition: *P* ≤ 0.20 and correlation coefficients >0.10; associations with the main result in CG: OR < 0.67 or OR > 1.5). Statistical adjustment to control for the impact of confounders on effect estimation will be applied by introducing them into the analyses (if changes in OR are greater than 10%). Effect modifiers of basal walking pattern will also be tested.

Multiple regression analysis will be performed for each secondary outcome variable. Baseline data will be introduced in the predictive model for each time measure. We will test the mediating effects of the behavioral intention and of implementation intentions in the total sample using path analysis.

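### Phase II treats women in group sessions of up to 10, but neither the sample size nor the named phase II models allow for correlation within sessions

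*Protocol article*

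**What the plan says.** On delivery, the Interventions section states: "The estimated duration of the intervention in each group is 90 minutes, conducted in only one group session with a maximum of 10 people". This applies to all three arms. The Randomization section has individual women allocated to arms within each patients' association, so the session is a unit of treatment and not of randomization.

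The Sample size calculation section works from expected rates ("The expected differential increase in the selected exercise prevalence from baseline is 10% for CG, 20% for IG and 40% for MIG"), a 5% α, 80% power and dropout. It arrives at a design in which "each group will consist of 115 persons, which is equal to 345 participants", and then "we added a 30% dropout rate as a reasonable calculation, which gives us a sample size of 449 women with FM". No ICC, session size or design effect appears.

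Under Statistical analysis, Phase II, the primary binary outcome is handled at each time point as follows: "backward stepwise logistic regression analysis will be applied". Change over time goes to a Cox model for recurrent events. For the rest, "Multiple regression analysis will be performed for each secondary outcome variable". No session effect, cluster-robust variance or generalized estimating equation (GEE) is mentioned.

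**The concern.** Women treated in the same session share the day, the researchers, the delivery and the group itself. The motivational theory used in the trial (Motivational intervention section) makes perceived social pressure a determinant of intention, so a group setting could plausibly move its members together. The named models, fitted in their ordinary form, treat women as independent. The recurrent-events model deals with repeated events in one woman, not with likeness between women in one session.

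If the within-session correlation is positive, intervals are too narrow, P values are too small, and the information in 115 women per arm is less than the calculation assumes. MIG against IG is one half of the main hypothesis, so a central comparison is exposed.

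**Working it through.** **Inputs from the article.** Rates CG 10%, IG 20%, MIG 40%; α 5%, power 80%; 115 per arm; at most 10 women per session; 274 women attended the first evaluation (Statistical analysis, Phase I), which is about 91 per arm if split evenly (274 / 3 = 91.3).

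**Assumed.** ICC 0.01, 0.02, 0.05. Session sizes m = 10 (the stated maximum), 7 (a full session after losing 30%) and 5. Two-sided tests; the article does not state sidedness.

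**1. The plan's own figure.** The standard two-proportion formula (pooled variance, no continuity correction) gives 199 per arm for 10% vs 20%, 82 for 20% vs 40% and 32 for 10% vs 40%. None is 115, and no variant tried with the stated α and power gave it. The last step does reproduce: 345 × 1.3 = 448.5, so 449. The failure to reproduce 115 is a separate matter. Here it matters only that no stated input is a clustering allowance.

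**2. Design effect and true size of a nominal 5% test.** DE = 1 + (m − 1) × ICC. True size = 2 × [1 − Φ(1.96 / √DE)]. For example, m = 10 and ICC 0.05 give DE = 1 + 9 × 0.05 = 1.45, √DE = 1.204, 1.96 / 1.204 = 1.628, and size 10.4%.

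| Women per session | DE at ICC 0.01 / 0.02 / 0.05 | True size |
|---|---|---|
| 10 | 1.09 / 1.18 / 1.45 | 6.0% / 7.1% / 10.4% |
| 7 | 1.06 / 1.12 / 1.30 | 5.7% / 6.4% / 8.6% |
| 5 | 1.04 / 1.08 / 1.20 | 5.5% / 5.9% / 7.4% |

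At m = 10 the true standard errors exceed those computed under independence by factors of 1.04 / 1.09 / 1.20.

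**3. Power of a test that does allow for sessions.** Effective n per arm = n / DE. Power = Φ{[d√n_eff − 1.96√(2p̄(1 − p̄))] / √[p₁(1 − p₁) + p₂(1 − p₂)]}, where d is the difference in rates and p̄ their mean. Check without clustering, 20% vs 40%, n = 115: (0.2 × 10.724 − 1.96 × 0.648) / 0.632 = 1.383, so power is 91.7%.

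| MIG vs IG (40% vs 20%) | No clustering | ICC 0.01 / 0.02 / 0.05 |
|---|---|---|
| 115 per arm, m = 10 | 92% | 89.2% / 86.7% / 79.0% |
| 115 per arm, m = 7 | 92% | 90.1% / 88.4% / 83.3% |
| 115 per arm, m = 5 | 92% | 90.6% / 89.5% / 86.2% |
| about 91 per arm, m = 10 | 84% | 81.2% / 78.0% / 69.2% |
| about 91 per arm, m = 7 | 84% | 82.3% / 80.2% / 74.0% |
| about 91 per arm, m = 5 | 84% | 83.0% / 81.6% / 77.4% |

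MIG vs CG (40% vs 10%) is lowest at about 91 per arm, m = 10, ICC 0.05. There n_eff = 91.3 / 1.45 = 63.0 and power is 98.0%. IG vs CG (20% vs 10%) has only 57% power at 115 per arm before any clustering, so its weakness does not come from this source.

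**4. Number of clusters.** 115 / 10 means at least 12 sessions per arm; 91 / 10 means at least 10.

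**The case against.** The strongest objection is that the ICC is wholly assumed and may be small. There is one 90-minute session, plans are written individually, each intervention component has its own researcher role, and walking is unsupervised and measured from week 7 to month 9. At ICC 0.01 the consequences are minor. This stands, and it makes the point conditional.

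Second, an article condenses, and an analysis plan could add a cluster-robust variance. It could. But the sample size is presented as complete and the models are named outcome by outcome, and as written neither reflects the delivery that the same article describes. The article does not claim independence in words; that follows from the models in their ordinary form.

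Third, sessions may not be wholly separate by arm. The caption of Figure 2 says that one researcher gives the walking information to all participants, and that the researcher delivering implementation intentions does not know which condition came before. The figure itself is not available. If some components were given to mixed arms, part of the shared effect cancels between arms and the design effect above overstates the problem. This stands and shapes the fix.

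Two arguments that a reader might add are not supported. Sessions drawn from a woman's own association would add further likeness, but the article does not say how sessions were composed. The Discussion's remark that participants might talk among themselves is raised as a threat to masking, through exchange about what each arm did. It is not evidence that women in one session become alike.

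**Conclusion.** The concern holds in a conditional form. Delivery in group sessions is fixed, and the sample size and the named phase II models make no allowance for it. Run as written, the analysis gives standard errors that are too small whenever the within-session correlation is positive. Over ICC 0.01 to 0.05 and 5 to 10 women per session, the true size of a nominal 5% test lies between 5.5% and 10.4%.

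A reader might infer that the trial loses its power. The figures do not support that for the MIG comparisons at the planned size: MIG vs CG stays at or above 98%, and MIG vs IG falls only to 79% in the least favourable case considered. The lower values for MIG vs IG (69% to 81% with 10 per session) combine clustering with the shortfall to 274 attendees, and the Discussion says that 180 further women would be contacted. The main concern is therefore error rate and interval width. All of this rests on assumed ICCs, on session sizes at or below the stated maximum, and on sessions being separate by arm.

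**What to change.** - Record the session each woman attended.
- In the phase II logistic, Cox and multiple regression models, use session as the cluster in all three arms. Use cluster-robust standard errors or GEE with a small-sample correction, or a random session intercept where it converges. Define the cluster as sessions were actually run, including any component given to mixed arms.
- Report the estimated ICC.
- State power over a range of ICCs and session sizes, using 1 + (m − 1) × ICC.

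The cost is one extra identifier, revised model wording and somewhat wider intervals. With about 10 to 12 or more sessions per arm and an expected control rate near 10%, a random-intercept logistic model may be unstable. In that case the small-sample-corrected robust errors should be used. If the ICC proves close to zero, little precision is lost.
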